### Randomization

Patients will be randomized into one of three study arms (arm A: endurance + resistance training, arm B: endurance training + breathing exercises, arm C: control group = usual care + exercise recommendation (following the guidelines of the American College of Sports Medicine)) using a web-based tool (https://randomizer.at). The allocation ratio is 2:1:1 for the first randomization into the control arm and two exercise arms followed by a 1:1 randomization of the original control group. Randomization is conducted after baseline assessment and is stratified based on the following two criteria to ensure balanced distribution of prognostic factors across all groups:

Histological stratification (non-squamous vs. squamous)

Squamous and non-squamous lung cancer differs by underlying biology, molecular characteristics, and response patterns to systemic therapy.

Forced expiratory volume in 1 s (FEV1)

FEV1 is a crucial measurement of lung function and is highly associated with VO_2_ peak. In advanced lung cancer patients, impairment of pulmonary function is common. FEV1 will be divided into two classifications: mild to moderate COPD—FEV1 is equal to or greater than 50% of predicted value and severe to very severe COPD—FEV1 is lower than 50% of predicted value.

The minimization method is used for stratified sampling [69]. Due to the nature of the intervention, participant blinding is not feasible. However, allocation concealment is ensured because the randomization sequence is generated and implemented through a secure, web-based system that prevents foreknowledge of group assignment. Outcome assessors conducting VO_2_ peak testing will remain blinded to treatment allocation. The randomization sequence was generated by an independent statistician. After baseline assessment, the responsible exercise scientist randomizes participants to the intervention groups using the secure, web-based randomization tool.

### Cardiopulmonary exercise testing

CPET will be carried out to assess the patient’s cardiopulmonary performance using the cycle ergometer in a semi-recumbent position. Through a breathing mask, inhaled and exhaled air can be analyzed, enabling a precise calculation of oxygen uptake (VO_2_) and carbon dioxide output (VCO_2_). To assess participants’ peak oxygen uptake (VO_2_ peak), a ramp protocol will be utilized. This diagnostic procedure is characterized by high precision in determining the anaerobic threshold through the ratio of VO_2_ to VCO_2_. The VO_2_ peak is considered a crucial factor in aerobic performance. Cardiopulmonary exercise testing also proves to be a safe diagnostic tool for advanced lung cancer patients [70].

### Physical function based on the hypothetical 1-repition maximum (h1-RM)

The one-repetition maximum (1RM) is a test to determine the maximum weight that the patient can move within a predefined range of motion. The test procedure for measurement of maximum strength is characterized by high reliability. As the one-repetition maximum represents an increased risk of injury in patients, there is the possibility of calculating the hypothetical one-repetition maximum (h1-RM). For this purpose, the Brzycki formula is used, and the maximum force can be calculated from this after the exercise and reduce the risk of injury or other adverse events [71].

### Questionnaires

The Functional Assessment of Chronic Illness Therapy—Fatigue (FACIT-Fatigue) questionnaire comprises 13 questions aimed at assessing self-reported fatigue and its impact on daily activities and physical function [72, 73]. The EORTC QLQ-C30/LC13 is a tumor entity-specific questionnaire designed to assess the quality of life in patients with lung cancer. The EORTC QLQ-C30/LC13 captures functional parameters (physical functioning, role functioning, cognitive functioning, emotional functioning), symptom scales (pain, fatigue, nausea, and vomiting), Global Quality of Life, and Global Health Status. Additionally, patients can indicate individual items that were symptomatic in the past week [74, 75]. The questionnaires are self-administered by patients at each time point; if study personnel need to assist, it will be documented in the trial’s management.

### Exercise adherence

Feasibility parameters including recruitment rate, dropout rate, and adherence to the training will be measured and documented by the responsible exercise therapist. All withdrawals will be considered as dropouts, with reasons noted and compared between each study arm. This provides a straightforward comparison of the raw dropout counts between groups. The percentage of participants who dropped out will also be calculated for each study arm relative to the total number of participants initially assigned to that arm. Adherence based on the absolute numbers of scheduled exercise sessions, both absolute and percentage-based adherence can be calculated and compared between study arms. Adherence to the protocol is defined as completing at least 75% of the possible training sessions.

### Interventions

Intervention (arm A) is a supervised exercise program combining endurance training and resistance training. Participants conduct two exercise sessions each week, with each session lasting 60 min. The breakdown of these sessions involves 20 min dedicated to endurance training and 40 min to resistance training. Aerobic interval training is characterized by an intensity set at 50% of the participants’ maximal workload, determined through CPET. This approach aims to optimize cardiovascular fitness through controlled and targeted aerobic exercises. Resistance training targets major muscle groups during each session. The exercise protocol prescribes two sets of each resistance exercise, with participants completing 8–12 repetitions per set. The training intensity for resistance exercises is progressively increased within a range of 50–80% of the participants’ h1-RM. This tailored approach allows for a progressive and adaptive response, ensuring that participants are appropriately challenged while minimizing the risk of overexertion. The initiation phase, scheduled for week one, is characterized by an intentional starting point at 30% of participants’ maximum capacity. The primary objective during this initial phase is to prepare the muscles for subsequent exertion while concurrently fostering an increased awareness of the body’s responses to the introduced exercise stimuli.

Arm B focuses exclusively on supervised aerobic exercise followed by breathing exercise. Participants in arm B engage in exercise twice per week, with each session lasting 30 min of intensity interval training. The endurance training in arm B adopts an interval-based method to strike a balance between exertion and recovery. The training intensity is set at 50% of the participants’ maximal workload and is increased during the intervention to 80% of maximal workload. The structured intervals involve 10 sets of 2 min of exertion alternated with 10 sets of 1 min for recovery, resulting in a total exercise time of 30 min per session. This design aims to challenge participants’ aerobic capacity while providing adequate recovery intervals. Following the aerobic intervals, participants perform 5 min of supervised pursed-lip breathing under the guidance of an exercise scientist, completing approximately 8–12 breathing cycles per minute three times. Additionally, patients will be performing 3 sets of 30 s of planks.

A pulse oximeter is employed for measuring heart rate and oxygen saturation to ensure safety. Additionally, the Borg-CR scale is utilized to assess subjective dyspnea after every second interval, providing a qualitative measure of perceived exertion and discomfort. Termination criteria are established to guide the conditions for stopping exercise within treatment arms: oxygen saturation <85% without increase during recovery and subjective increase in Borg-CR scale indicating severe dyspnea.

The control group receives a one-time physical activity consultation with general information about daily activities and exercise participation, as well as individual training recommendations. After 12 weeks, the control group will be randomized into one of the exercise groups.

#### Concomitant care and co-interventions

All participants will continue to receive standard medical care throughout the study, and no clinically indicated treatment will be restricted. All medications will be documented using ATC codes to enable transparent post hoc evaluation of potential influences on exercise capacity or cardiopulmonary outcomes. Nutritional intake—including oral nutritional supplements, protein products, or energy-dense formulations—will not be restricted, acknowledging the high prevalence of cancer-associated weight loss and the ethical necessity of supporting adequate nutrition in this population. Existing physiotherapy or rehabilitation programs may continue if they were established prior to enrollment and remain unchanged in frequency, type, and intensity. To minimize contamination of the intervention effect, participation in other exercise trials and the initiation of high-intensity exercise programs outside the study period are discouraged but not prohibited. This approach ensures both ethical feasibility and scientific transparency. Overall, the trial prioritizes comprehensive documentation rather than restriction of concomitant care to reflect real-world clinical practice in advanced lung cancer.

### Metabolic fingerprinting

Venous blood (EDTA) and urine samples from all participants are collected at the onset of the first session and subsequently every 12 weeks until the conclusion of the study. Both sample types are subjected to centrifugation at 900 ×g at 4 °C for 10 min, and the resulting supernatant is stored at −80 °C for future analysis.

For metabolomic analysis, the samples are diluted with specific urine and plasma diluents, and sodium trimethylsilylpropanesulfonate is added as an NMR standard. NMR-based metabolomics provides a quantitative platform to profile baseline metabolic alterations in advanced lung cancer and to assess how exercise modulates systemic pathways (e.g., amino acid, lipid, and energy metabolism) in order to explore links between metabolic patterns, physiological adaptation, and clinical outcomes. Laboratory analyses are restricted to non-genetic biochemical and physiological measurements. No genomic, germline, or whole-genome analyses will be performed. Laboratory staff receive only a pseudonymized participant ID, with no access to identifiable data. All procedures follow institutional governance and quality-control standards. There is no planned future use of samples within the main study. Samples will be analyzed only for the metabolic evaluations described in the protocol, and no additional storage for other research is intended. Some patients, however, have signed a separate optional consent allowing their samples to be used in a related translational research project (e.g., potential proteomic analyses/metabolomics). Any such work will be conducted under a separate ethics approval and according to applicable governance requirements.

### Evaluation of the intervention and patient-centered interviews

Quantitative and qualitative data are collected as part of the evaluation process [76]. The quantitative component focuses on participants’ satisfaction with various aspects of the exercise intervention. A self-developed online questionnaire assesses elements such as the structure and delivery of the intervention, organizational aspects, and support provided by the trainer team. Responses are recorded on a five-point Likert scale (“strongly disagree” to “strongly agree”), and sociodemographic information is also collected. Open-ended items allow participants to elaborate on their responses and provide detailed feedback. The survey is distributed to all participants, and data are analyzed descriptively. Frequency distributions, means, medians, standard deviations, and modes describe satisfaction levels and variability. Subgroup comparisons (e.g., age, intervention format) help identify potential differences. Free-text responses are analyzed using qualitative content analysis [77, 78], enabling systematic coding and inductive category development.

The qualitative component consists of episodic interviews with a purposive sample of approximately 15 participants. While participants are comparable in terms of their underlying medical condition, the sample is deliberately selected to reflect diversity in other relevant characteristics. Selection is based on factors such as age, gender, and symptom burden to capture a broad range of experiences.

The number of interviews is guided by data saturation and may be adjusted as needed. The interviews explore perceived changes in quality of life, physical well-being, self-efficacy, and sustained physical activity. The episodic format captures both specific experiences and broader reflections. Transcripts are analyzed using qualitative content analysis according to Kuckartz [77], a method well suited to identifying thematic patterns in narrative data.

Findings from both components are expected to inform the development and refinement of future exercise interventions. Combining structured satisfaction data with personal narratives supports improvements that are both evidence-informed and participant-centered [79, 80].

### Sample size calculation

The sample size calculation is based on the primary endpoint of the improvement in VO_2_ peak after 12 weeks (t_1_) compared to baseline (t_0_). Using a study by Quist et al. [81], where VO_2_ peak was measured in patients with advanced lung cancer before and after a 6-week exercise therapy, an assumed mean difference of 0.1 is considered between the exercise therapy groups and the control group. Additionally, a standard deviation of 0.18 is assumed [80]. With a one-sided *t*-test assuming equal variances at a significance level of 0.05 and a power of 0.80, 41 patients are required in the control group and 41 patients in the exercise therapy groups. Considering that approximately 15% of deaths are expected after 24 weeks due to disease progression [82], a dropout rate of 20% is assumed, resulting in the inclusion of 52 patients per group (52 patients in the control group, 26 patients in arm A, and 26 patients in arm B). The 52 patients of the control group will also be randomized to one of the treatment arms, resulting in also 52 patients per treatment arm for the comparison of arm A vs. arm B for the secondary objective. All secondary analyses, including the secondary objective, are exploratory, so that the sample size calculation is only based on the primary objective.

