### Objectives

The primary objective is to achieve an improvement in aerobic capacity (VO_2_ peak) from t0 to t1 through exercise therapy compared to the standard of care. As a secondary objective, we aim to examine whether there is a difference between the two exercise therapies regarding the performance improvement (VO_2_ peak) from the beginning of the therapy to the end of the therapy (either t2 compared to t1 or t1 compared to t0, depending on the randomization arm). Other secondary objectives are to assess changes in quality of life, fatigue, dyspnea during the study participation and evaluation adherence to the intervention, dropout rates, adverse events, and tumor therapy response.

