## Methods and design

BREATH is a prospective 3-arm randomized controlled trial (RCT) including histologically confirmed advanced NSCLC (UICC stages IIIB, IIIC, and IV) patients during palliative anti-cancer treatment. Patients in stage IIIB and IIIC will only be enrolled if potentially curative treatment options were excluded. Enrollment started in June 2024 and is estimated to be open for 2.5 years (Fig. 1). Study participants will be divided into study arms using a 2:1:1 randomization, with one control group and two exercise therapy groups. Participants in the two intervention arms will undergo exercise therapy, with one group receiving individual endurance training with additional breathing exercise and the other group receiving a combination of endurance and resistance training. Both intervention groups will exercise supervised twice a week for 12 weeks. The control group will initially undergo standard of care for 12 weeks. Afterwards, the patients in the control group will be randomized into one of the two intervention arms and will also receive treatment twice a week for 12 weeks. This approach has the advantage of providing a sufficiently large sample for both comparing overall exercise therapy with the control group and comparing the two types of exercise therapy. In addition, this design allows all participating patients to receive exercise therapy. By individually measuring the hypothetical one-repetition maximum (h1-RM) and conducting cardiopulmonary exercise testing (CPET) on a cycle ergometer, a tailored individual training program based on current performance will be offered to the patient. BREATH exercise begins with moderate exertion and is progressively increased during the course of the study participation (see Interventions for a detailed description). Outcome measurement will be at baseline (t_0_), after 12 weeks (t_1_), and after 24 weeks (t_2_), leading to a maximum study participation of 6 months (Fig. 1). The Ethics Committee of the Medical Faculty University of Duisburg-Essen approved this study (22–10522-BO) in December 2023 (Table 1).

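### The 52 patients per arm stated for arm A vs arm B assumes that no control is lost before the week-12 re-randomisation, against the dropout assumed in the same paragraph

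*Protocol article*

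**What the plan says.** The Sample size calculation section of the protocol article sizes the trial on the 12-week comparison of exercise with control. It finds that with "a power of 0.80, 41 patients are required in the control group and 41 patients in the exercise therapy groups". It then cites mortality, "approximately 15% of deaths are expected after 24 weeks due to disease progression", sets dropout at 20%, and arrives at 52 controls and 26 patients in each of arms A and B. The next sentence has all 52 controls randomised again, "resulting in also 52 patients per treatment arm for the comparison of arm A vs. arm B for the secondary objective".

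Methods and design, and Interventions, both place this second randomisation after the 12-week control period. Randomization gives its ratio as 1:1. Objectives defines the A-vs-B outcome as the change over each patient's own exercise block: "either t2 compared to t1 or t1 compared to t0, depending on the randomization arm". Methods and design presents the delayed-start layout as "providing a sufficiently large sample for both comparing overall exercise therapy with the control group and comparing the two types of exercise therapy".

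Data analysis applies intention to treat to primary and secondary endpoints. Death or worsening is handled as worst case, and other missing endpoint data above 5% by multiple imputation. All secondary analyses, A vs B included, are labelled exploratory, and details are left to a statistical analysis plan.

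**The concern.** For the primary comparison, 52 is a number randomised, and losses come afterwards. For A vs B, the controls' first 12 weeks of loss come before they are allocated to A or B. The paragraph treats the two situations alike. It inflates 41 to 52 because patients will be lost, and then counts all 52 as still present when they are re-randomised.

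The analysis rules cannot close the gap. A control who dies or withdraws before week 12 has no arm to be analysed in. Worst-case handling and imputation supply a missing outcome, not a missing allocation.

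At stake are the stated size of the named secondary objective and one of the two advantages claimed for the design. Stating the same 52 as for the primary comparison invites the reader to think that both comparisons start from equal numbers. They do not.

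**Working it through.** **Inputs, all from Sample size calculation unless noted.** Difference: "an assumed mean difference of 0.1 is considered between the exercise therapy groups and the control group". Spread: "a standard deviation of 0.18 is assumed". One-sided t-test, "assuming equal variances at a significance level of 0.05 and a power of 0.80". Dropout 20%. Deaths about 15% by week 24. First allocation 52 control, 26 A, 26 B. Second allocation 1:1 at week 12 (Randomization; Interventions).

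**Step 1: reproduce the primary figures.**
- n per group = 2 × (1.645 + 0.842)² × 0.18² / 0.1² ≈ 40.1, rounded up to 41. Exact power from the noncentral t distribution at 41 per group is 0.802.
- 41 / 0.80 = 51.25, rounded up to 52 per group, 104 in total.

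These match the plan.

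**Step 2: reproduce the A-vs-B figure.**
- 26 + 52/2 = 52 per arm.

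This matches only if every control reaches week 12 and is re-randomised.

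**Step 3: allow for loss before re-randomisation.** Let d be the proportion of controls lost by week 12.
- Controls re-randomised = 52 × (1 − d)
- Allocated per arm = 26 + 52 × (1 − d)/2

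The plan does not say whether its 20% covers 12 or 24 weeks. The primary calculation applies it to a week-12 endpoint, but the reason given is 24-week mortality. Three readings follow; the second and third assume a constant rate over 24 weeks.

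| Reading | d | Re-randomised | Allocated per arm | Shortfall from 52 |
|---|---|---|---|---|
| 20% lost by week 12 | 0.200 | 52 × 0.800 = 41.6 | 26 + 20.8 = 46.8 | 5.2 |
| 20% lost over 24 weeks | 1 − √0.80 = 0.106 | 52 × 0.894 = 46.5 | 26 + 23.3 = 49.3 | 2.7 |
| 15% deaths over 24 weeks, no other loss | 1 − √0.85 = 0.078 | 52 × 0.922 = 47.9 | 26 + 24.0 = 50.0 | 2.0 |

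These are numbers allocated, before any further loss during the exercise block.

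**Step 4: scale of the consequence.** The plan gives no expected difference between A and B. Borrowing the primary values (0.1, SD 0.18, one-sided 0.05) for scale only, and with everyone allocated contributing an outcome, power is 0.88 at 52 per arm and 0.85 at 46.8 per arm.

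**The case against.** The best defence is that A vs B is exploratory. The plan bases its sample size on the primary objective alone and claims no power for this comparison. Sufficiently large has no threshold attached, and 47 to 50 allocated per arm is still more than the 41 required for the primary comparison. All of this stands and limits the consequence. It does not make 52 a number that the design can be expected to deliver.

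A second defence is that 52 is an inclusion number before dropout, as in the primary comparison. That is a fair reading, and it is why the comparison above is with numbers allocated. It does not rescue the figure, because controls lost before week 12 are missing from the allocated count itself. It could also be said that some patients counted as dropouts remain available, since the retention section keeps inviting patients who have not withdrawn consent. Even so, deaths alone bring the figure to about 50.

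Two stronger readings are tempting, and the documents do not support either.

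- **A large evaluable shortfall.** A reader might take a further 20% off in the exercise block and arrive at 26 × 0.8 + 20.8 × 0.8 = 37.4 evaluable per arm. That applies the 20% twice, which means 36% loss among controls over 24 weeks, although the plan ties its 20% to 15% deaths at 24 weeks. The plan also never calls the 52 evaluable, and after allocation its worst-case and imputation rules keep lost patients in the analysis.
- **An analysis that ignores randomisation stage.** A reader might infer this because changes from t0 to t1 are pooled with changes from t1 to t2 and no stage term is named. But Data analysis plans multivariable regression without listing the A-vs-B covariates, and leaves details to an analysis plan that is not shown. Allocation between A and B is 1:1 at both stages, so leaving stage out would mainly cost precision and would not confound the comparison. Any figure for lost precision needs a between-stage difference that the documents do not give.

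**Conclusion.** The stated 52 per arm is wrong as written. It is an upper bound that requires no control death or withdrawal in the first 12 weeks, contrary to the attrition assumed in the same paragraph. The expected number allocated is about 47 per arm if the 20% applies by week 12, and 49 to 50 if the 20% or the 15% deaths runs evenly over 24 weeks. The overstatement is thus about 2 to 5 patients per arm. The lower end rests on the constant-rate assumption, and on deaths being the only loss.

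The effect is modest. The primary figures of 41, 52 and 104 reproduce and stand, and A vs B remains exploratory. The correction is still worth making because A vs B is the named secondary objective and its sample size is offered as an advantage of the design.

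**What to change.** 1. In Sample size calculation, replace the 52 per arm with the expected numbers: about 42 controls re-randomised and 47 allocated per arm if the 20% applies by week 12, or about 46 to 48 re-randomised and 49 to 50 allocated per arm if loss is spread over 24 weeks. State that these are before any further loss in the exercise block.
2. Say whether the 20% covers 12 or 24 weeks.
3. Define the A-vs-B intention-to-treat set as patients actually allocated to A or B, at either randomisation. Controls lost before week 12 stay in the primary comparison only.
4. Qualify the sample-size claim in Methods and design to match.
5. Optional: include randomisation stage (initial or delayed) as a covariate in the A-vs-B regression, if the analysis plan does not already do so. This is a recommendation for precision, not the correction of a proven error.

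The cost is a few sentences and, if taken up, one covariate. No patients are added and the primary analysis does not change.
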